# Causal impact of DNA methylation on refracture in elderly individuals with osteoporosis – a prospective cohort study

**DOI:** 10.1186/s12891-024-07521-y

**Published:** 2024-06-03

**Keywords:** Osteoporosis, Vertebral compression fracture, Vertebral augmentation, Refracture, DNA methylation

## Abstract

**Background:**

Osteoporotic vertebral compression fractures (OVCF) in the elderly increase refracture risk post-surgery, leading to higher mortality rates. Genome-wide association studies (GWAS) have identified susceptibility genes for osteoporosis, but the phenotypic variance explained by these genes has been limited, indicating the need to explore additional causal factors. Epigenetic modifications, such as DNA methylation, may influence osteoporosis and refracture risk. However, prospective cohorts for assessing epigenetic alterations in Chinese elderly patients are lacking. Here, we propose to conduct a prospective cohort study to investigate the causal network of DNA polymorphisms, DNA methylation, and environmental factors on the development of osteoporosis and the risk of refracture.

**Methods:**

We will collect vertebral and peripheral blood from 500 elderly OVCF patients undergoing surgery, extract DNA, and generate whole genome genotype data and DNA methylation data. Observation indicators will be collected and combined with one-year follow-up data. A healthy control group will be selected from a natural population cohort. Epigenome-wide association studies (EWAS) of osteoporosis and bone mineral density will be conducted. Differential methylation analysis will compare candidate gene methylation patterns in patients with and without refracture. Multi-omics prediction models using genetic variants and DNA methylation sites will be built to predict OVCF risk.

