The objective of this study is to investigate the genetic and epigenetic markers associated with osteoporosis and bone mineral density, and their impact on refracture risk among elderly patients. We aim to collect vertebral body blood and peripheral blood samples from 500 patients with OVCF who will undergo detailed clinical assessments, genome-wide genotype and methylation profiling at baseline. Following the surgical intervention, these patients will be followed up for 1 year to monitor refracture events, during which clinical and genome-wide methylation data will be collected again. These valuable data will enable us to identify genetic and epigenetic markers that can predict OVCF and refracture risk in the elderly and develop accurate prediction models.

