### Sample size

The power of EWAS is essential for detecting differentially methylated positions (DMPs) between cases and controls. Similar to GWAS, the power of EWAS depends on four key factors, including study design, sample size, effect size, and burdon of multiple test correction. Previous simulation analysis has shown that a sample of 500 cases and 500 controls would achieve 80% power to detect differential methylation at epigenome-wide significance (*P* < 1E-6) with a methylation odds ratio of 1.28 or mean methylation differences of 5% in case–control designs of EWAS (cite the original pubication) [19]. Therefore, we aim to recruit 500 elderly patients with OVCF who underwent vertebral augmentation surgery, as well as 500 healthy controls matched for age, gender, and race from the CAS cohort who did not develop OVCF or osteoporosis. This sample size will provide adequate statistical power for detecting significant differences in DNA methylation levels between cases and controls and enable us to identify epigenetic markers associated with refracture after vertebral augmentation surgery for OVCF.

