### Biomarker identification and prediction analysis

The GWAS of bone mineral density will be carried out in PLINK using linear regression model, assuming an additive allele effect. Covariates for age, gender, drug usage and the first five principal components to account for residual population structure will be also included in the model. The genomic control inflation factor will be used to adjust the *p*-values. The adjusted *p*-values equal to or smaller than 5E − 8 will be considered as genoome-wide significant. We will conduct a GWAS using case–control design to invesgate the genetic variants associated with osteoporosis.

This study will use whole-genome methylation data from vertebral and peripheral blood samples of 500 osteoporosis patients with recurrent fractures after vertebral augmentation and 1000 natural population controls from the Chinese Academy of Sciences. To identify differentially methylated positions (DMPs) between patients with and with out refracture, we will perform an epigenome-wide association study (EWAS) and meQTL analysis. Patients with refracture who underwent vertebral augmentation will be selected as cases, and an equal number of patients without refracture will be selected as controls based on age range and epidemiological indicators such as BMI, disease, and medication history. We will analyze changes in methylation levels of osteoporosis- and bone mineral density-related sites in elderly patients with refracture within one year after surgery. The R language DMRfinder package will be used for analysis, and functional annotation of the identified DMPs and differentially methylated regions (DMRs) will be performed.

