### Clinical implications/impact of the study

The systematic analysis of molecular mechanisms underlying osteoporosis and bone mineral density phenotypes is of great importance, and this study aims to explore cross-omics molecular markers that affect these phenotypes based on multi-omics data and the degree of physiological aging. The research objectives of this study include:Conducting genome-wide association analysis and genome-wide epigenetic association analysis of osteoporosis and bone mineral density to identify genetic and epigenetic molecular markers related to these phenotypes and to deeply analyze their molecular mechanisms.Evaluating the feasibility of DNA methylation in assessing the effect of postoperative intervention for osteoporosis by analyzing changes in methylation levels of bone mineral density related sites in elderly patients with refracture after vertebral augmentation for OVCF within one year after surgery.Improving the risk prediction model of osteoporosis by considering multiple factors such as genetic variation and environmental factors, which can provide a scientific basis for the molecular classification and prevention of related diseases and serve as a paradigm for biomedical researchers conducting multi-omics life data research.

The results of this study can provide valuable insights into the molecular mechanisms of osteoporosis and bone mineral density phenotypes, which can facilitate the development of effective interventions and personalized treatments. The findings can also contribute to the establishment of a risk prediction model for osteoporosis that takes into account genetic and environmental factors, which can help identify individuals at high risk for developing osteoporosis and enable targeted preventive measures. Overall, this study has the potential to make significant contributions to the field of osteoporosis research and improve clinical practice in the management of related diseases.

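### In the patient-versus-healthy-control methylation scan, every case and no control is sampled around a fracture and its surgery, so fracture-episode effects can be taken for osteoporosis markers

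*Protocol article*

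**What the plan says.** The Abstract (Methods) fixes when patients give blood: "We will collect vertebral and peripheral blood from 500 elderly OVCF patients undergoing surgery". The Background calls this the baseline profile: "genome-wide genotype and methylation profiling at baseline".

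The comparators are described in the Abstract as follows: "A healthy control group will be selected from a natural population cohort". The Sample size section defines them as "500 healthy controls matched for age, gender, and race from the CAS cohort who did not develop OVCF or osteoporosis". The section on biomarker identification gives a different count, "1000 natural population controls from the Chinese Academy of Sciences".

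The contrast is presented in the Abstract as an epigenome-wide scan for osteoporosis and bone mineral density. The first research objective, under Clinical implications, is "to identify genetic and epigenetic molecular markers related to these phenotypes". The methylation sites found are then predictors in the models for bone mineral density and OVCF risk (end of the biomarker section).

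A repeat profile is planned. The Background says of the one-year follow-up: "during which clinical and genome-wide methylation data will be collected again". The only stated use of change over time is in patients with refracture, as a way of judging postoperative intervention (biomarker section, Clinical implications, Advanced features). Table 1 lists no methylation sample at any visit.

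**The concern.** Two things separate the cases from the healthy controls: osteoporosis, and a vertebral fracture serious enough to be operated on. As the 500 patients are described, both are present in every case, and both are absent from the controls by selection. Matching on age, gender and race does not touch this, and no covariate can separate two factors that never vary independently within a contrast.

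The plan does not treat methylation as fixed, since it proposes to study change within a year of surgery. A site that moves because of the fracture episode (injury response, pain, immobility) would pass the scan as readily as a lasting correlate of osteoporosis. Such a site would then enter the prediction model, where it would be of little use for people who have not yet fractured. If it later returned towards normal, it could be misread again as a response to postoperative treatment.

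The plan already intends to collect data bearing on this but describes no analysis that uses them for the purpose.

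**Working it through.** **1. Do case status and the fracture episode overlap completely?**

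| | OVCF patients (baseline) | Healthy CAS controls |
|---|---|---|
| Osteoporosis | yes | no, by selection |
| Vertebral fracture treated by augmentation | yes | no, by selection |
| Sampled around that operation | yes | no |
| Matched on | age, gender, race | age, gender, race |

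No cell contains osteoporosis without the fracture episode, or the episode without osteoporosis. The healthy-control contrast alone cannot tell them apart.

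**2. The plan's own power figure.** Inputs from Sample size: 500 per group, P < 1E-6, 80% power, mean difference 5 points (0.05). No SD is given and sidedness is not stated; I assume a two-sided test and the normal approximation. The SD that yields 80% is then:

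- standardised effect = (4.892 + 0.842) × √(2/500) = 5.733 × 0.06325 = 0.363
- implied SD = 0.05 / 0.363 = 0.138

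The 80% is therefore consistent with an SD of about 0.138, but cannot be reproduced from the text.

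**3. Chance that a site unrelated to osteoporosis is flagged.** Let b be a shift present in all cases because of the fracture episode. The probability of passing P < 1E-6 is Φ(b/SE − 4.892), with SE = SD × √(1/n₁ + 1/n₂). Both b and SD are assumptions, shown as ranges, for 500 v 500:

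| SD | b = 2 points | 3 points | 4 points | 5 points |
|---|---|---|---|---|
| 0.138 | 0.5% | 7% | 38% | 80% |
| 0.10 | 4% | 44% | 92% | 99.9% |
| 0.05 | 92% | >99.9% | >99.9% | >99.9% |

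With no shift the rate is 0.0001%. With 1000 controls and SD 0.138, SE = 0.138 × √(1/500 + 1/1000) = 0.00755, and a 5-point shift is flagged with probability Φ(6.62 − 4.89) = 96%. More controls make the scan more sensitive to either cause; they do not help to tell the causes apart.

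**4. What the later comparison could show.** The Background quotes refracture rates of 6.2% to 51.8% from the literature. Applied to 500 patients as an illustration, that is 31 to 259 refractures, leaving 469 to 241 patients without one, before losses. Against 500 controls with SD 0.138, the power for an undiminished 5-point difference at P < 1E-6 is:

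- 469 patients: SE = 0.00886, Φ(5.64 − 4.89) = 77%
- 241 patients: SE = 0.01081, Φ(4.62 − 4.89) = 39%

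A site can therefore miss the threshold at the later sample only because fewer patients contribute. The two time points should be compared on estimates and intervals, not on whether each passes 1E-6.

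**The case against.** **No evidence of a transient effect.** A reader might infer that fracture effects will in fact be reported as osteoporosis markers. The documents do not support that. They do not show that such effects exist, how large they are or that they fade, and they give no interval from fracture to surgery. The supported statement is that the design cannot exclude them. Step 3 says only that any shift of a given size is detected equally well whatever its cause; it gives no share of false markers, and nothing in the documents would supply one.

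**Other comparisons.** A reader might extend the point to the whole study. It does not extend to refracture versus no refracture, where both groups had a fracture and surgery. Nor would a scan of bone mineral density within patients be fully mixed with fracture status.

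**Eligibility wording.** The T ≤ -2.5 criterion is listed as a separate numbered item and could be read as admitting osteoporosis without fracture. The Abstract, Background and Sample size sections, however, describe all 500 as OVCF patients having surgery. Some sections also describe the cases as patients who have already refractured, which needs reconciling; on either reading they are sampled around a fracture.

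**Adjustment elsewhere.** White blood cell count is recorded, and an analysis plan not shown may adjust for cell composition. That would deal with only part of the difference.

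**The later sample is imperfect.** This objection stands. Patients follow individual anti-osteoporosis programmes, so a difference that disappears may reflect treatment rather than healing. It rules out barring such sites from the prediction model.

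**Conclusion.** The concern holds for the comparison of OVCF patients with healthy controls. Cases and controls differ in osteoporosis and in the fracture episode together, and the plan states no analysis that would help to separate the two. A 5-point shift from the episode alone would be flagged with 80% probability at 500 v 500, and with about 96% against 1000 controls. These figures assume a two-sided test and the SD of 0.138 implied by the plan's own power statement. The number of affected sites is unknown.

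It would go too far to conclude that the reported markers will be artefacts, or that a site which fades is thereby shown to be one. The point merits a change because the repeat profiling already announced allows a useful, though not decisive, check.

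**What to change.** - **Table 1:** enter the repeat peripheral-blood methylation sample and state its time point. The text places it only within the follow-up year.
- **Biomarker identification and prediction analysis:** add a second patient-versus-control comparison using that sample, primarily in patients without refracture, against the same controls.
- **Reporting:** for each site significant at surgery, give the estimated difference and its interval at both time points. Describe sites that differ only at surgery as not separable from the acute fracture episode or from postoperative treatment, rather than as established osteoporosis markers.
- **Prediction model:** report it with and without those sites; do not exclude them outright.

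The cost is a little more analysis, provided that the repeat profiling covers patients without refracture, as the Background indicates. The drawback is that true markers may shrink at the later sample because of anti-osteoporosis treatment. Patients without refracture are also a subset selected on outcome, which should be stated beside the result.

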**Discussion:**

This study will be the first large-scale population-based study of osteoporosis and bone mineral density phenotypes based on genome-wide data, multi-time point methylation data, and phenotype data. By analyzing methylation changes related to osteoporosis and bone mineral density in OVCF patients, the study will explore the feasibility of DNA methylation in evaluating postoperative osteoporosis intervention effects. The findings may identify new molecular markers for effective anti-osteoporosis treatment and inform individualized prevention and treatment strategies.

**Trial registration:**

chictr.org.cn ChiCTR2200065316, 02/11/2022.

**Supplementary Information:**

The online version contains supplementary material available at 10.1186/s12891-024-07521-y.

## Background

Osteoporotic vertebral compression fractures (OVCF) are the most common fracture type in patients with osteoporosis, accounting for about half of osteoporosis-related fractures [1]. These fractures are associated with high morbidity and mortality [2], and vertebral augmentation is the standard operation for their treatment. While vertebral augmentation has significant effects in relieving pain and restoring vertebral height [3], it cannot fundamentally cure the fracture and prevent recurrence. Furthermore, the literature reports that the rate of recurrence of OVCF after vertebroplasty is high [4], ranging from 6.2% to 51.8% [5]. The debate on the risk factors of refracture after vertebral augmentation has lasted for nearly 20 years, but it is still inconclusive.

Osteoporosis is a complex disease caused by both genetic and environmental factors. While hundreds of genes and loci associated with osteoporotic fractures or bone mineral density have been identified through genome-wide association studies (GWAS), these can only explain a small proportion of the variation in the disease and its manifestations. For example, the 20 genes found in *GEFOS-1* explain only 5% of the phenotypic variation [6]. The hundreds of loci identified by the GWAS of bone mineral density based on UK biobank samples could only explain 12% to 20% of the phenotypic variation [7]. Therefore, the susceptibility genetic loci of osteoporosis found by GWAS alone cannot achieve accurate prediction of phenotypic changes, and even the prediction model based on a large number of genetic loci cannot achieve the accuracy required for practical applications in clinics.

Epigenetic modifications, including DNA methylation and histone modification, affect cell differentiation and development by affecting the structure and expression of genes, thereby regulating the genetic risk and environmental influence of various complex phenotypes and diseases [8]. Therefore, DNA methylation modification is considered as a bridge connecting genotypes and individual phenotypes. Epigenome-wide association studies (EWAS) of bone mineral density have discovered methylation sites playing a significant role in the pathogenesis of osteoporosis [9–15]. Furthermore, previous studies have revealed that exercise intervention for osteoporosis may achieve its effects by modulating the expression of bone metabolism genes via alterations in DNA methylation levels [16–18].

The objective of this study is to investigate the genetic and epigenetic markers associated with osteoporosis and bone mineral density, and their impact on refracture risk among elderly patients. We aim to collect vertebral body blood and peripheral blood samples from 500 patients with OVCF who will undergo detailed clinical assessments, genome-wide genotype and methylation profiling at baseline. Following the surgical intervention, these patients will be followed up for 1 year to monitor refracture events, during which clinical and genome-wide methylation data will be collected again. These valuable data will enable us to identify genetic and epigenetic markers that can predict OVCF and refracture risk in the elderly and develop accurate prediction models.

## Methods

### Recruitment of patients

This will be a prospective multicenter cohort study conducted in 5 medical centers, including Peking University International Hospital, Beijing Tiantan Hospital affiliated to Capital Medical University, Beijing Changping District Hospital, Tengzhou Central People’s Hospital, and Linfen People’s Hospital. The study was approved by the Biomedical Ethics Committee of Peking University International Hospital (batch number: 2022-KY-0010-01). Recruitment of elderly patients with OVCF after vertebral augmentation and those without refracture will take place from December 2022 to December 2023. All participants will provide informed consent. The flow chart is presented in Fig. 1. An example of refracture in elderly individuals with osteoporosis who undergo vertebral augmentation is shown in Fig. 2.

**Fig. 1 Fig1:**
[figure not shown]
Flowchart of this trial. OVCF: osteoporotic vertebral compression fracture

### Sample size

The power of EWAS is essential for detecting differentially methylated positions (DMPs) between cases and controls. Similar to GWAS, the power of EWAS depends on four key factors, including study design, sample size, effect size, and burdon of multiple test correction. Previous simulation analysis has shown that a sample of 500 cases and 500 controls would achieve 80% power to detect differential methylation at epigenome-wide significance (*P* < 1E-6) with a methylation odds ratio of 1.28 or mean methylation differences of 5% in case–control designs of EWAS (cite the original pubication) [19]. Therefore, we aim to recruit 500 elderly patients with OVCF who underwent vertebral augmentation surgery, as well as 500 healthy controls matched for age, gender, and race from the CAS cohort who did not develop OVCF or osteoporosis. This sample size will provide adequate statistical power for detecting significant differences in DNA methylation levels between cases and controls and enable us to identify epigenetic markers associated with refracture after vertebral augmentation surgery for OVCF.

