For the whole-genome microarray genotyping data, we will use the Infinium Asian Screening Array + MultiDisease -24 (ASA-MD) genotyping chip. Genome Studio software will be used for quality control of raw data. Samples with a call rate less than 99% and SNPs with a call rate less than 98% will be filtered out. After quality control, PLINK software will be used for further processing. Samples with kinship will be excluded by calculating the Identity-By-Descent (IBD) and inbreeding coefficient (F). Imputation and preprocessing will be performed based on the 1000 genomes of the East Asian population and the Han population genome of the previous study. SNPs that do not meet the Hardy–Weinberg equilibrium (HWE ≥ 0.001) and minor allele frequency (MAF ≥ 0.01) will be excluded.

For the genome-wide methylation beadchip data, DNA from vertebral and peripheral blood samples stored at -80 °C will be bisulfite converted, and the Infinium MethylationEPIC BeadChips (Illumina) will be used for genome-wide DNA methylation profiling. BeadChips will be processed according to the manufacturer’s protocol, and then imaged using the iScan Microarray Scanner (Illumina). The resulting idat files will be processed using the CHAMP Bioconductor package. Samples with missing probes greater than 10% and probes missing in samples more than 20% will be removed, and KNN imputation will be carried out for the rest. Probes with less than three beads in more than 5% of samples and non-CpG, cross-reactive, or non-specific probes will also be removed. Probes mapping on the sex chromosomes and contained SNPs will also be removed. After checking sample outliers by MDS plots and beta values distribution of Type-I and Type-II, data normalization will be performed using BMIQ. Samples with genotype data will be kept, and methylation beta values will be transformed into M values.

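### The quoted 80% power matches neither control number in the article: it leaves no room for the planned sample filters with 500 controls, and is too low with 1000

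*Protocol article*

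**What the plan says.** The Sample size section of the protocol article reports that "a sample of 500 cases and 500 controls would achieve 80% power to detect differential methylation at epigenome-wide significance". The threshold is P < 1E-6 and the effect is a methylation odds ratio of 1.28 or a mean methylation difference of 5%. From this it derives its own target: "we aim to recruit 500 elderly patients with OVCF who underwent vertebral augmentation surgery", together with "500 healthy controls matched for age, gender, and race from the CAS cohort who did not develop OVCF or osteoporosis". It concludes that this size is sufficient.

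The laboratory text under Survey contents and methods then sets sample-level filters. Samples with a genotype call rate below 99% are dropped, and related samples are excluded. For the methylation arrays, "Samples with missing probes greater than 10% and probes missing in samples more than 20% will be removed". Last, "Samples with genotype data will be kept", so a person whose genotyping fails also leaves the methylation analysis. Outliers are checked, but no rule for removing them is given. No expected loss and no replacement of failed samples is stated.

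Two later sections, Biomarker identification and prediction analysis and Advanced features of this study, put the controls from the Chinese Academy of Sciences cohort at 1000.

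**The concern.** The simulated 500 per group is most naturally a count of samples with usable data, although the article does not say so. The recruitment target equals that count, so with 500 controls any sample removed by the filters takes power below 80%. If 1000 controls are analysed, the figure is wrong in the other direction. This is the only power figure in the article, and readers will use it to judge how far a null result at a site can be trusted. As written, they cannot tell whether the chance of detecting the stated effect is nearer 70% or above 90%.

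**Working it through.** **Inputs from the article.** 500 cases and 500 controls, 80% power, P < 1E-6 and a 5% mean difference (Sample size); 1000 controls (the two later sections).

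**Assumptions.** A two-sided normal test of two means with the same SD in both groups, and loss rates of 1% to 20%. The article gives neither the SD nor the loss rates.

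**The plan's own figure.** The 80% comes from a cited simulation whose variance model is not shown, so it cannot be reproduced independently. In a two-means calculation, 500 per group gives 80% for a 5% difference only if the SD is about 0.138. An SD of 0.10 would give 99.9%, and 0.15 would give 65%. I therefore accepted the 80% as stated, calibrated the effect to it, and varied only the group sizes.

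**Formula.** Let h be the harmonic mean of the group sizes, h = 2·n1·n2/(n1 + n2). The non-centrality at 500:500 is 4.892 + 0.842 = 5.733 (rounded from unrounded values). Then

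power = Φ(5.733 × √(h/500) − 4.892).

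For example, at 450:450, h = 450 and 5.733 × √0.9 = 5.439. Then 5.439 − 4.892 = 0.547, and Φ(0.547) = 70.8%.

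| Controls planned | Loss assumed | Cases:controls analysed | h | Power |
|---|---|---|---|---|
| 500 | none | 500:500 | 500 | 80% (calibrated) |
| 500 | 1% in both groups | 495:495 | 495 | 79.2% |
| 500 | 2% in both groups | 490:490 | 490 | 78.4% |
| 500 | 5% in both groups | 475:475 | 475 | 75.7% |
| 500 | 10% in both groups | 450:450 | 450 | 70.8% |
| 500 | 20% in both groups | 400:400 | 400 | 59.3% |
| 500 | 5% in cases only | 475:500 | 487.2 | 77.9% |
| 500 | 10% in cases only | 450:500 | 473.7 | about 75% |
| 1000 | none | 500:1000 | 666.7 | 95.8% |
| 1000 | 10% in both groups | 450:900 | 600 | 91.8% |
| 1000 | 20% in both groups | 400:800 | 533.3 | 84.8% |

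With 500 controls, the shortfall exceeds 2 points once about 2.5% of both groups is lost. With 1000 controls, 80% needs only 1/(2/500 − 1/1000) ≈ 333 analysed cases. A one-sided threshold changes little: 71.0% instead of 70.8% at 10% loss in both groups.

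**Expressed as a detectable difference.** At 80% power the detectable difference scales as 5% × √(500/h):

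- 450:450 gives 5% × √(500/450) = 5.27%.
- 500:1000 gives 5% × √(500/666.7) = 4.33%.
- 450:900 gives 5% × √(500/600) = 4.56%.

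**The case against.** A reader might infer that the study will fall short of its stated power. The documents do not support that. No loss rate is given, and below about 2.5% loss in both groups the shortfall is under 2 points. The rows at 10% and 20% show sensitivity and are not forecasts. If 1000 controls are analysed, power stays above 80% even after 20% loss in both groups.

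Three more points for the plan stand:

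- The 80% is attributed to earlier simulation work. For this study the article claims only that power is sufficient, and a fall of 2 to 4 points would not refute that.
- The controls come from an existing cohort. The 1000 may be the pool from which 500 matched controls are drawn, and failed controls may be replaced. The article says neither, and its analysis section lists the methylation data of 1000 controls. If replacement is intended, the rows for loss in cases only apply, and they still fall below 80%.
- The filters overlap, because the call-rate filter and the genotype requirement partly remove the same people. Their losses should not be added as if independent.

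A reader might also count deaths and non-response during the year of follow-up, or outlier removal, against the 80%. Neither belongs here. The baseline samples are already in hand when follow-up starts, and the article only checks for outliers.

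The objection that an allowance for loss could sit in a fuller protocol has some weight. It does not settle the matter, because the article itself prints the power figure, derives the target from it, and gives two control numbers.

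**Conclusion.** The point holds as a mismatch between a printed power figure and the design described around it, not as proof of an underpowered study. The 80% is correct only for 500 cases and 500 controls with no sample lost. With 500 controls it is an upper limit: about 78% at 2% loss in both groups, 76% at 5% and 71% at 10%. With 1000 controls it is an understatement: about 96% without loss and 92% at 10% loss in both groups. The direction of the error cannot be settled until the control number is. These sizes rest on the article's own 80% as calibration, a two-sided normal comparison of means, and assumed loss rates. They concern only the baseline comparison of patients with healthy controls.

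**What to change.** 1. Reconcile the control number across Sample size, Biomarker identification and prediction analysis, and Advanced features of this study. If 1000 is a pool and 500 the matched set, say so, and say whether controls that fail quality control are replaced.
2. State the expected proportion of samples passing all filters, for cases and for controls, and label it as an assumption.
3. Restate the power, or the minimum detectable difference at 80% power, of the baseline comparison of patients with healthy controls for those numbers. A short range, such as 2%, 5% and 10% loss, is enough.

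The cost is a few sentences and one recalculation. Recruitment need not change. With 500 controls the printed figure becomes somewhat less favourable; with 1000 it becomes more favourable.

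### The 80% power in the sample-size section applies to OVCF patients against healthy controls; it does not support the refracture claim, where a 500-patient cohort gives at most 250 per group and about 20% power

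*Protocol article*

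**What the plan says.** The Sample size section cites earlier simulation work in which "a sample of 500 cases and 500 controls would achieve 80% power to detect differential methylation" at P < 1E-6, for a "methylation odds ratio of 1.28 or mean methylation differences of 5" per cent. It applies this as follows: "we aim to recruit 500 elderly patients with OVCF who underwent vertebral augmentation surgery", set against 500 healthy people from the natural population cohort who have neither OVCF nor osteoporosis. It concludes that this size is adequate for case-control differences in methylation and will also "enable us to identify epigenetic markers associated with refracture after vertebral augmentation surgery for OVCF".

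The refracture comparison is defined under Biomarker identification and prediction analysis. Refracture patients are the cases, and "an equal number of patients without refracture will be selected as controls based on age range and epidemiological indicators". The same section calls the analysis epigenome-wide. The Abstract describes it more narrowly: "Differential methylation analysis will compare candidate gene methylation patterns in patients with and without refracture".

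The Abstract and the last paragraph of the Background describe one group of 500 operated OVCF patients followed for a year. The only refracture rate in the article is a literature range in the Background, "ranging from 6.2% to 51.8" per cent. No expected number of refractures is stated.

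**The concern.** Healthy people who never had the operation carry no information on who refractures after it. The 80% therefore belongs to one contrast, and the refracture clause relies on another that is drawn from inside the 500 patients and is necessarily smaller. Refracture is the title question and a stated objective. If the sample-size paragraph is taken at face value, readers will believe the refracture scan can find effects of the planned size. If it cannot, a scan without hits says little about such effects.

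**Working it through.** **Inputs.** From Sample size: 500 per group, 80% power, P < 1E-6, mean difference 5 points. From Biomarker identification: 1:1 selection for refracture. From Background: refracture 6.2% to 51.8%. Not given: the SD, the baseline methylation level, and whether the test is one- or two-sided. A two-sided test and a normal approximation are assumed.

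**Step 1. The plan's own figure.** Without an SD, the 80% cannot be reproduced independently. It can be used to back-solve the standardised effect d:

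d = (z for 1 − α/2 + z for 80%) × √(2/n) = (4.892 + 0.842) × √(2/500) = 0.363.

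For a 5-point difference this implies an SD of 5/0.363 = 13.8 points. Entering d again at 500 v 500 returns 80%.

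**Step 2. Ceiling for the refracture contrast, without assuming any refracture rate.** A 1:1 split of 500 patients cannot exceed 250 v 250.

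Power = Φ(d/√(1/n₁ + 1/n₂) − 4.892) = Φ(0.363/√(2/250) − 4.892) = Φ(4.05 − 4.89) ≈ 20%.

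A one-sided test gives 21.3% and a noncentral-t calculation 19.4%.

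**Step 3. With assumed refracture rates among 500 patients.** The 1:1 group size is the smaller of the two counts. It peaks at a 50% rate, not at the top of the literature range.

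| Assumed rate | Refracture / none | 1:1 groups | Power, 1:1 | Power, all non-refracture patients as comparators |
|---|---|---|---|---|
| 6.2% | 31 / 469 | 31 | 0.03% | 0.2% |
| 20% | 100 / 400 | 100 | 1.0% | 5.0% |
| 30% | 150 / 350 | 150 | 4.0% | 12.0% |
| 40% | 200 / 300 | 200 | 10.3% | 17.9% |
| 50% | 250 / 250 | 250 | 20.1% | 20.1% |
| 51.8% | 259 / 241 | 241 | 18.1% | 20.0% |

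**Step 4. Effect detectable with 80% power, as a multiple of the planned effect.** The multiple is √[(1/n₁ + 1/n₂)/(2/500)].

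- All non-refracture patients as comparators: 31 v 469 gives √(0.0344/0.004) = 2.9; 100 v 400 gives √(0.0125/0.004) = 1.8; 250 v 250 gives √(0.008/0.004) = 1.4.
- 1:1 selection: 31 v 31 gives √(500/31) = 4.0; 100 v 100 gives √(500/100) = 2.2; 250 v 250 gives 1.4.

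**Step 5. Who the 500 are.** The Abstract, Background and Sample size sections describe 500 operated OVCF patients in all. The Eligibility criteria make recurrent fracture part of entry, and Biomarker identification describes 500 patients with recurrent fractures. On that second reading, 500 refractures with an equal number of operated patients without refracture would need about 500 + 500 = 1000 operated patients. The first three sections do not provide them, and the control-group inclusion criteria give no number.

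**The case against.** **The text does not state 80% for refracture.** This stands. Adequate power is asserted for cases against controls, and the refracture clause says only that markers can be identified. A reader might infer that the protocol claims 80% at epigenome-wide significance for refracture, but the words do not go that far. They do make the sample size the basis for identifying refracture markers, and the one calculation offered does not bear on that.

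**The refracture counts are not the protocol's.** This also stands. The 6.2% to 51.8% is a literature range, not a planning value, and is not tied to one year. It would be wrong to say that the comparison has a particular number of patients. The ceiling of 250 per group needs no rate.

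**Power depends on an SD that is not given.** True. If the SD were 10 points, 241 v 241 would have 72% power for a 5-point difference. But 500 v 500 would then have 99.9%, not the stated 80%. Keeping to the stated 80% fixes the effect near 0.36 SD under the approximation used. Nothing here shows that the 80% is wrong for its own contrast.

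**There may be 500 refracture cases.** Two sections read that way, and a 500 v 500 refracture contrast would then be conceivable. It needs about twice the operated patients that the other sections provide, and the written justification would still concern healthy controls.

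**A candidate-gene comparison would face a lighter multiplicity burden.** Yes, but the article gives no list, number of sites or threshold for it, and the sample-size argument does not use it.

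**Conclusion.** Wrong as written. The power statement is carried from OVCF against healthy controls to a refracture contrast that it does not cover. With 500 operated patients in total, the refracture contrast has at most 250 per group and about 20% power at the protocol's threshold. If the literature range is assumed to apply, groups run from 31 to 250 and power from about 0% to 20%; using every non-refracture patient as a comparator gives about 0.2% to 20%. These percentages are illustrative. They assume the same standardised effect for refracture as for OVCF, back-solved with a two-sided normal approximation. The mismatch of contrasts and the 250 ceiling do not depend on that effect; the ceiling depends only on 500 being the total. The article's conflicting descriptions of the 500 are part of the problem and do not rescue the claim.

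**What to change.** 1. Limit the 80% statement to OVCF patients against healthy controls.
2. Delete the refracture clause, or replace it with a statement specific to that contrast. For example: with 500 operated patients and all non-refracture patients as comparators, the difference detectable with 80% power at P < 1E-6 is about 2.9, 1.8 and 1.4 times the planned effect at assumed refracture rates of 6.2%, 20% and 50%. If 1:1 selection is kept, the multiples are about 4.0, 2.2 and 1.4.
3. Label the epigenome-wide refracture scan exploratory.
4. Reconcile the Abstract, Background and Sample size sections with the Eligibility criteria and Biomarker identification sections on whether the 500 are all operated OVCF patients or only those with refracture, and state the number without refracture.

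The cost is rewording and a less favourable power statement. No extra patients are needed.
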